# INTERPRETing to increase access to PSYcho-oncology care (INTERPRET-PSY) for cancer patients with limited English proficiency: study protocol for a pilot randomized controlled trial

**DOI:** 10.1186/s40814-026-01770-5

**Published:** 2026-01-29

**Keywords:** Limited English proficiency, Psycho-oncology, Feasibility studies, Telemedicine, Counseling, Survivorship

## Abstract

**Background:**

People with cancer who have limited English proficiency (LEP) are at high risk for poor mental health outcomes in survivorship as they face cultural, linguistic, and mobility-related barriers to accessing psychosocial care. Telemental health interventions can be of great utility because they can decrease participation burden and are cost-effective. Patients with LEP who receive telemental health services primarily access them through remote interpretation due to a shortage of bilingual therapists. Remote interpreting can be: (1) simultaneous (rarely used in medical settings) or consecutive (usual care in medical settings). Prior research has found that Remote Simultaneous Medical Interpreting (RSMI) resulted in fewer errors, better medical outcomes, and higher patient satisfaction than consecutive methods in oncology and primary care settings. Yet, RSMI has not been studied in the context of a counseling/psychotherapy encounter. INTERPRET-PSY is a mixed method, 3-arm pilot randomized controlled trial (RCT) designed to determine if RSMI is feasible and acceptable in comparison to usual care (RCMI) and “gold standard” care (bilingual provider) in delivering counseling/psychotherapy to Mandarin-speaking LEP cancer patients.

**Methods:**

A total of 45 participants will be randomly assigned to one of 3 arms (*n* = 15 RCMI, *n* = 15 RSMI, and *n* = 15 bilingual provider) to receive 6 counseling/psychotherapy sessions. Feasibility and acceptability of the interpreting modalities (RCMI, RSMI) will be evaluated through self-report assessments. Secondary outcomes will include therapeutic alliance, MCP-Ch content comprehension, and clinically significant interpreting errors across the interpreting (RCMI, RSMI) arms. Semi-structured interviews with a purposively sampled subset of patients, their interventionists, and interpreters (if applicable) across all 3 arms will assess potential barriers and facilitators to successful interpreter-mediated communication and outcomes.

**Discussion:**

INTERPRET-PSY is the first study to examine the feasibility and acceptability of delivering a culturally adapted, evidence-based, and telehealth-delivered counseling/psychotherapy intervention to cancer patients with LEP via RCMI and RSMI. Results of the pilot RCT will be submitted for publication in a peer-reviewed journal and serve as preliminary data for a larger, multisite RCT grant application for a fully powered RCT of interpreting modalities in the provision of linguistically accessible and culturally appropriate psycho-oncology care.

**Trial registration:**

NCT02112188

**Supplementary Information:**

The online version contains supplementary material available at 10.1186/s40814-026-01770-5.

## Background

More than 67 million people in the U.S. speak a language other than English at home and more than 26 million (8% of the population) have limited English proficiency (LEP) [1]. While most people with LEP are immigrants, nearly 19% were born in the U.S., most to immigrant parents [2]. People with LEP are anticipated to reach 19% of the U.S. population by 2050 [1].

This fast-growing population is at disproportionate risk for poor cancer outcomes. Patients with LEP (immigrant or US-born) are less likely to access preventive medical care, such as cancer screenings and regular medical visits [3, 4], due to financial, cultural, and linguistic barriers to healthcare access and navigation [5]. For example, they may delay seeking care to avoid communication difficulties, out of concern about the costs of medications or copayments, or because they doubt their needs will be adequately addressed by healthcare providers [6]. These disparities in preventive care contribute to higher cancer mortality rates, as suggested by a meta-analysis that found immigrant women were more likely to present with breast cancer at an advanced stage than native-born women [7]. Although the meta-analysis did not examine language as a factor in stage at diagnosis, findings indicated that immigrants from countries with developed economies experienced the most similar stage distribution to native-born populations, suggesting immigrants from developing nations—who are also more likely to have LEP—may face more financial or access-related barriers to care than those from developed nations [7]. Indeed, a study of physicians treating LEP breast cancer patients found 75% of physicians reported using untrained interpreters [8], which has been shown to result in more errors of clinical consequence [9]. Given these disparities in cancer outcomes and care, individuals with LEP may be especially susceptible to poor psychosocial outcomes in survivorship. Research indicates that foreign-born, ethnoracial minority, LEP, and lower-income cancer patients are more likely to report higher levels of distress and poorer quality of life than native-born, non-Hispanic White, English proficient, and higher-income patients [10–12].

Psychosocial interventions show significant promise in improving quality of life and emotional adjustment outcomes for cancer patients. However, the vast majority of intervention trials have been conducted in predominantly non-Hispanic White (NHW) English-speaking, and middle-to-high income samples [13]. Our systematic review and meta-analysis of psychosocial interventions for immigrant and LEP cancer patients found only 9 psychotherapy/counseling interventions available to non-English speakers. Of these, only 3 were delivered by telephone, despite our finding that in-person and telephone-delivered interventions were equally effective [14]. Given the potential physical mobility issues that all cancer patients face, as well as competing time burdens and systemic barriers to accessing mental health care common among immigrant and LEP patients, telemental health interventions, which can decrease participation burden and are typically more cost-effective to implement, may be of great utility in this population [15, 16]. Past research suggests high telehealth engagement potential among LEP patients, with rates of intervention adoption over 65% when they were specifically tailored for LEP patients [17, 18].

The majority of patients with LEP who access mental health care do so through medical interpreters, given a national shortage of bilingual mental health professionals [19]. Typically, medical interpretation is consecutive (interpreting is provided once a speaker has finished speaking) [20]. RSMI or “United Nations-style” interpreting is similar to a voice-over and is provided remotely by trained medical interpreters [20]. RSMI is likely superior to consecutive interpreting methods due to increased efficiency [21, 22], fewer clinically significant medical errors [21, 22], and enabling a more private and dyadic clinical encounter [21, 23]. By contrast, the most commonly employed interpreting strategy, Remote Consecutive Medical Interpreting (RCMI), can interfere with the collaborative relationship between patient and therapist (i.e., therapeutic alliance) [24], one of the most robust predictors of psychosocial intervention outcomes [25]. In addition, consecutive interpreting can impede the natural flow of communication, as interpreters pace their interlocutors. Yet to our knowledge, RSMI has not yet been studied in the telemental health context; a systematic review on the use of interpreters in mental health found no quantitative studies on interpreter accuracy nor on the influence of interpretation modes on the therapist–patient relationship [26].

To address these limitations, INTERPRET-PSY is a mixed method, explanatory sequential (QUANT qual), 3-arm pilot randomized controlled trial (RCT) developed to determine whether RSMI is feasible and acceptable in comparison to usual care (RCMI) and “gold standard” care (bilingual provider) in delivering psycho-oncology counseling to Mandarin-speaking Chinese cancer patients with LEP.

## Methods

### Overview and theoretical framework

The study is guided by the Behavioral Model for Vulnerable Populations (BMVP), which identifies factors that influence the health-seeking behavior of “vulnerable” or medically underserved populations [27]. Predisposing factors such as limited English proficiency, immigration status, and acculturation level may lead to a decrease in seeking healthcare. Enabling factors, such as the availability of linguistically appropriate care and community resources, facilitate health-seeking behaviors. Our study seeks to address predisposing factors and maximize enabling factors to increase access to needed psychosocial care among cancer patients with LEP (Fig. 1).

**Fig. 1 Fig1:**
[figure not shown]
Aims, procedures, outcomes, and theoretical framework of the INTERPRET-PSY study

The methods for INTERPRET-PSY were developed in accordance with the Standard Protocol Items: Recommendations for International Trials (SPIRIT) guidelines [28]. Any prospective amendments to the protocol, eligibility, or outcomes will first be approved by MSK’s Institutional Review Board.

### Key study objectives

Assess the feasibility of interpreting modes in delivering counseling sessions to Chinese cancer patients with LEP. RSMI and RCMI feasibility will be determined by the completion of ≥5 out of 6 sessions for *n* = 11 per arm (*primary outcome*). We will also collect descriptive data on recruitment/randomization/retention rates; acceptability (*secondary outcome*); and telehealth usability for all 3 arms.Collect pilot data on outcomes central to RSMI and RCMI-enabled psycho-oncology counseling. We will summarize post-intervention scores on therapeutic alliance (Working Alliance Inventory), treatment expectancy (i.e., the degree to which participants expect a good outcome from counseling), and counseling content comprehension by arm (RSMI, RCMI, bilingual provider), and will compare the number of clinically significant interpreting errors in MCP-Ch Session 1 across RSMI and RCMI arms *(secondary outcomes)*. We will also summarize post-intervention scores on psychosocial outcomes (e.g., distress, spiritual well-being, quality of life, anxiety and depression, meaning in life, and hopelessness) by arm (*exploratory outcomes*).To inform “best practices” in telehealth delivery of interpreter-mediated psycho-oncology care. We will complement quantitative outcome data with qualitative data from semi-structured interviews with *n*~ 8 “extreme responders” (~6 per arm, pending saturation) and their interventionists and interpreters (if applicable). Interviews will contextualize outcomes and identify barriers and facilitators to interpreter-mediated communication in counseling.

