## Outcomes

The first goal of INTERPRET-PSY is to determine the feasibility of using RSMI and RCMI to deliver a manualized, culturally adapted counseling intervention to LEP cancer patients. Participants will be deemed not evaluable for feasibility if they drop out prior to Session 6 due to non-intervention related issues (e.g., progression of cancer or death). These non-evaluable participants will be replaced and reasons for dropout tracked. A determination of feasibility for RSMI/RCMI (*primary outcome*) will be met if *n* = 11 complete treatment (a comparable 67% MCP completion rate was achieved in [name] original MCP trial [35]), defined as completing 5 out of 6 sessions (i.e., ≥11 out of 15 participants completing ≥5/6 sessions). We will also calculate the observed recruitment rate, retention rate, participant satisfaction with treatment protocol (*secondary outcome*, scored by calculating the percentage of positive “agree” responses on a satisfaction survey), and telehealth usability in all 3 arms (RSMI, RCMI, bilingual provider). These outcomes will be measured quantitatively within 1 month following the intervention (T8) through a post-intervention assessment.INTERPRET-PSY also will assess the effect of interpreter-mediated delivery on counseling/psychotherapy process outcomes. This will be measured by comparing the RSMI and RCMI groups to the “gold standard” bilingual provider group at post-intervention assessment (T8), administered within 1 month following the intervention. Outcomes will include therapeutic alliance, MCP-Ch content comprehension, and the number and nature of clinically significant interpreting errors in MCP-Ch Session 1 (*secondary outcomes*); participants’ treatment expectancy, post MCP-Ch session 1 (T2); and distress, spiritual well-being, quality of life, anxiety and depression, meaning in life, and hopelessness (*exploratory outcomes*). We will also assess post-session ratings after each MCP-Ch session (T2, T3, T4, T5, T6, and T7).We will identify barriers and facilitators to successful interpreter-mediated delivery of MCP-Ch in semi-structured interviews with “extreme responders” in each of the 3 arms (i.e., participants who score especially high or low on therapeutic alliance, MCP-Ch comprehension, and/or acceptability). These will be assessed approximately 3 months post-intervention (T9).

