## Measures

A description of each quantitative measure used at each assessment is provided in Table 2, and a timeline of assessments is provided in Table 3. Most measures have demonstrated good reliability and validity in Mandarin-speaking populations (Table 2). Surveys that do not have validated Chinese translations will be translated and checked for quality by qualified translators using an established five-step process for translation and evaluation developed by Forsyth et al. [39]. All measures will be administered either by phone or videoconference by trained bilingual research staff and entered into REDCap, a secure web platform for electronic data capture.

**Table 2 Tab2:** List of assessments

Measure Title	Time Points Used	Outcome	Description of Measure
Demographic and Clinical Characteristics	T1 (Baseline)	n/a	Age (years), gender, race, ethnicity, education, preferred language, level of English proficiency, country of origin, immigration length, frequency of revisiting birthplace, employment status, household income, marital status, household size, religious/spiritual beliefs, health insurance status, most recent cancer diagnosis, and current cancer treatment received
Digital Health Care Literacy (DHCL) [40]	T1 (Baseline)	n/a	The DHCL is a brief (3-item), face valid measure of one’s confidence in the ability to use technological programs or services and the ability to independently troubleshoot technical issues. Cronbach’s α = 0.90 [36]
Feasibility	T8 (Post-intervention)	Primary	Feasibility will be assessed via attendance logs and defined as ≥11 out of 15 participants completing ≥5/6 sessions
Acceptability	T8 (Post-intervention)	Secondary	A 20-item, investigator-initiated, face-valid survey to assess participants’ satisfaction with the intervention, mode of delivery (via RSMI or bilingual interventionist) and effects of treatment (i.e., whether the intervention was helpful). Acceptability will be scored by calculating the percentage of positive (“agree”) responses
Therapeutic Alliance (WAI-S) [41]	T2, T3, T4, T5, T6, T7 (Post-sessions 1–6)	Secondary	The Working Alliance Inventory-Short Form (WAI-S) is a 12-item self-report scale of therapeutic alliance with 2 forms: one for the client, and one for the interventionist. Cronbach’s α = 0.86. [42]*

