### Post-session assessments (T2, T3, T4, T5, T6, T7)

Therapeutic Alliance (WAI-S) [41], Weekly Session Rating and Telehealth Evaluation

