### Post-intervention assessment (T8) administered within 1-month post-intervention

Distress Thermometer (DT) [44], Spiritual Well-Being (FACIT-Sp) [46], Quality of Life (MQOL) [48], Anxiety and Depression (HADS) [50], Meaning in Life (MLQ) [52], Beck Hopelessness Scale (BHS) [54], Telehealth Usability (TSQ) [56], Acceptability, MCP-Ch Concept Comprehension, and Exit Survey

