### Data analysis plan (by objective)

Counseling completion rates will be calculated; we will treat each interpreting arm (RSMI, RCMI) as a single stage design and will assess each separately for feasibility (*primary outcome*). We will calculate frequencies and percentages to summarize recruitment, randomization, retention, acceptability (*secondary outcome*), and usability across all 3 arms (RSMI, RCMI, and bilingual provider). Based on the calculation outlined by Khan, Sarker, and Hackshaw [58], observing 11 or more successes out of 15 in a given arm would allow us to be sufficiently confident that the population feasibility of the corresponding interpretation mode is 90% against a null of 40%. In our calculations, we have set our statistical power to 90% and our Type I error rate to 0.025 to reduce the chance of false discovery. This provides us with sufficient combined statistical power, assuming the two tests are independent.We will summarize (1) therapeutic alliance scores and MCP-Ch content comprehension at T4 across all 3 arms (RSMI, RCMI, and bilingual provider) and (2) number and nature of clinically significant interpreting errors in MCP-Ch Session 1 across the interpreting arms (RSMI, RCMI) (*secondary outcomes*). We will also summarize treatment credibility/expectancy at T2 and differences in post- vs. pre-intervention distress, spiritual well-being, quality of life, anxiety and depression, meaning-in-life, hopelessness by arm (*exploratory outcomes*). These descriptive summaries by arm will provide preliminary indications of whether delivery of psycho-oncology counseling via RSMI or RCMI may potentially achieve clinically significant benefits, which will aid in the design of, and be further assessed in, a subsequent fully powered trial [29]. We will assess baseline contextual factors at T1 (e.g., digital health care literacy, level of English proficiency) to examine whether therapeutic alliance and MCP-Ch content comprehension scores differ by these variables. We will use an error analysis tool developed by Gany et al. [21] to obtain the number and nature of clinically significant errors in MCP-Ch Session 1. Specifically, a panel of 2–4 psycho-oncology clinicians blinded to the interpreting method (i.e., RSMI or RCMI) will review and code transcripts. They will independently code each script to identify clinically significant content and meet to reconcile any differences in their selection of clinically significant content. Examples of potentially clinically significant content include history of cancer diagnosis, past psychiatric history, MCP-Ch session exercises, and plans for future visits. Once all clinically significant content has been identified, a second blinded panel of 2–4 bilingual coders will independently code clinically significant content to identify interpreting errors, yielding a total count of clinically significant interpreting errors. To ensure rigor, coders on both panels will first separately conduct preliminary analyses on a subset of transcripts using the described protocol. Interrater reliability will be assessed by calculating percent agreement. Consensus meetings will be held to adjudicate disagreements and refine error categories and the analytic approach as needed until strong interrater reliability is reached (i.e., *k* = 0.80), at which point coders will commence coding of the remaining transcripts.To assess our semi-structured interviews with “extreme responders,” we will use thematic content analysis [59] to derive insights directly from participants’ narratives, following established guidelines for conducting rigorous qualitative research [60]. First, coders will each read a subset of interviews and develop codes to characterize responses. Coders will then meet to establish an initial codebook, which will be used to code the remaining interviews. Regular consensus meetings will be held to confirm the reliability of coding. The codebook will be iteratively revised as new codes emerge, and codes will be summarized into themes. Prominent themes will include those observed across the majority of interviews as well as key divergences between sub-groups. Findings will be integrated using NVivo [61], which enables qualitative and quantitative data to be paired by participant and in summary format. The coded qualitative data will be explored in relationship to participant outcomes, baseline characteristics, contextual factors, and study arm to further elucidate barriers and facilitators to the implementation of remote interpreting in the psycho-oncology setting.

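### Therapeutic alliance is rated only after attended sessions, but its by-arm summary is tied to one inconsistently stated time point, so early stoppers with existing ratings drop out of it

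*Protocol article*

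**What the plan says.** All references are to the protocol article.

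**When alliance is measured.** Table 2 (Measures) schedules the WAI-S at "T2, T3, T4, T5, T6, T7 (Post-sessions 1–6"). The list of post-session assessments agrees: "Therapeutic Alliance (WAI-S) [41], Weekly Session Rating and Telehealth Evaluation". The list for the T8 post-intervention assessment gives the psychosocial scales and then ends "Telehealth Usability (TSQ) [56], Acceptability, MCP-Ch Concept Comprehension, and Exit Survey"; the WAI-S is not in it.

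**When alliance is summarised.** Three places give a time, and they differ.
- Key study objectives, objective 2: "We will summarize post-intervention scores on therapeutic alliance (Working Alliance Inventory").
- Outcomes, second goal: the process outcomes, alliance among them, are measured by "comparing the RSMI and RCMI groups to the “gold standard” bilingual provider group at post-intervention assessment (T8").
- Data analysis plan, second objective: "We will summarize (1) therapeutic alliance scores and MCP-Ch content comprehension at T4 across all 3 arms".

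**What the summaries are for.** The analysis plan says "These descriptive summaries by arm will provide preliminary indications of whether delivery of psycho-oncology counseling via RSMI or RCMI may potentially achieve clinically significant benefits", and that they will help to design the fully powered trial. Alliance scores, high or low, are also one of the criteria for choosing interviewees (Outcomes; Qualitative interviews).

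**The concern.** A rating given after a session exists only if the session took place. Someone who stops after session k therefore has k ratings at most and nothing later. A summary at one fixed point drops that person, even though earlier ratings are in the database.

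The loss may be informative. The Background says that consecutive interpreting "can interfere with the collaborative relationship between patient and therapist (i.e., therapeutic alliance) [24], one of the most robust predictors of psychosocial intervention outcomes". If some participants stop because the alliance is poor, their low scores leave the arm in which the difficulty arose. The replacement rule in Outcomes covers people who drop out before session 6 for reasons unrelated to the intervention, such as progression or death. Those who stop because of the intervention or its delivery are not replaced, so they are the ones left without a later score.

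Two uses are exposed: the by-arm alliance figures that go forward to the next trial, and the selection of low-alliance participants for interviews about barriers. A participant with no score at the chosen point cannot be picked out as low-alliance at that point.

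**Working it through.** **1. Test each stated time against the collection schedule.** By the article's labels, T2 is post-session 1, T4 is post-session 3, T7 is post-session 6, and T8 is the assessment within one month after the intervention.

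| Time used for the summary | Who has no score |
|---|---|
| T8 (Outcomes) | Everyone: no WAI-S is listed at T8 |
| T7 (a possible reading of post-intervention) | Anyone who misses session 6, including someone who attends sessions 1 to 5 and so meets the 5-of-6 completion definition |
| T4 (analysis plan) | Those who stop after session 1 or 2, who have one or two ratings |

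No choice of label keeps every rated participant. Table 3 is a figure and could not be read here, so the statement about T8 rests on Table 2 and the two assessment lists.

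**2. How much stopping the design accepts.** The plan gives no figure for alliance. Its only calculated figure is the feasibility cut-off, 11 of 15, and this reproduces. By exact binomial with n = 15, P(X ≥ 11 | 0.40) = 0.0093 and P(X ≥ 11 | 0.90) = 0.987. A cut-off of 10 would give 0.0338, above 0.025. A feasible arm may therefore have 15 − 11 = 4 non-completers, 4/15 = 27%.

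**3. Shift in one arm's mean.** Let d be the share without a score and ρ the correlation between alliance and staying on a normal latent scale. The documents give no ρ, so every value here is an assumption. The mean among those who remain rises by

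shift = ρ · φ(z_d) / (1 − d), in SD units, with z_d the d-quantile of the standard normal.

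- d = 4/15: z = −0.623, φ = 0.3286, and 0.3286 / 0.7333 = 0.448.
- d = 2/15: z = −1.111, φ = 0.2153, and 0.2153 / 0.8667 = 0.248.
- d = 1/15: z = −1.501, φ = 0.1293, and 0.1293 / 0.9333 = 0.139.

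| d | ρ = 0 | ρ = 0.3 | ρ = 0.5 | ρ = 1 |
|---|---|---|---|---|
| 4/15 | 0 | 0.134 | 0.224 | 0.448 |
| 2/15 | 0 | 0.075 | 0.124 | 0.248 |
| 1/15 | 0 | 0.042 | 0.069 | 0.139 |

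**4. Difference between arms.** This is what a reader would compare.
- 4/15 against 1/15, a late time point: 0.448 − 0.139 ≈ 0.310 SD at ρ = 1. This gives 0, 0.093 and 0.155 SD at ρ = 0, 0.3 and 0.5, in favour of the arm with more stopping.
- 2/15 against 1/15, an assumed pattern for T4: 0.248 − 0.139 ≈ 0.110 SD at ρ = 1. This gives 0, 0.033 and 0.055 SD at ρ = 0, 0.3 and 0.5.
- Equal stopping and equal ρ in both arms: 0.

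For scale, the standard error of a difference between 11 and 14 participants is √(1/11 + 1/14) = 0.40 SD.

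**The case against.** The strongest reply is that the documented error is the conflict over the time point. Once that is settled, what remains is the handling of missing ratings and a choice about repeated measures, which a condensed article may leave to the full protocol or SAP. Part of this stands: the amount of selection depends on how the conflict is resolved, and a model specification would normally sit in the SAP. But the point does not rest on an absent missing-data method. The article itself fixes a single-point summary for an outcome whose existence depends on attendance, and step 1 shows that every candidate point loses someone who has been rated.

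Four further limits are accepted.
- T4 is mid-treatment. A reader of the objectives alone might infer that alliance is always summarised late; the analysis plan does not support that, and at T4 fewer participants would be lost.
- Not every use of alliance has a fixed time. The contextual-factor analysis, the interview selection and the descriptive summary in the Discussion name none, so the article does not establish that the other ratings are discarded.
- A reader might infer that the arm with more stopping will look better. That needs stopping to be related to low alliance and to differ between arms. The article gives neither stopping rates by arm nor a correlation, and the Background does not say that low alliance causes stopping.
- The 0.448 SD in step 3 is a worst case within one arm, with a perfect relation between alliance and stopping and a large-sample formula. It is not a difference between arms.

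Session completion is also reported by arm as the primary outcome for the interpreting arms, so an imbalance in stopping between them would be visible. That helps interpretation but does not bring the lost ratings back into the summary.

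**Conclusion.** The point holds in a limited form. The three statements of the summary time contradict one another, and the one at T8 has no scheduled WAI-S behind it. Whichever collected time is kept, a single-point summary leaves out early stoppers who have ratings.

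Bias in favour of the arm with more stopping is possible, not shown. Under the assumed correlations of 0.3 to 0.5 and 4/15 against 1/15 stopping, it is 0.093 to 0.155 SD; it is zero if alliance and stopping are unrelated, and smaller at T4 if few stop before session 3. These sizes are below the sampling error of a comparison at this sample size.

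Alliance is secondary and descriptive. No test, sample size or go/amend/stop rule depends on it. What is affected is the quality of the pilot data on alliance and the selection of interviewees. The change is worth making because it is cheap and the ratings are already collected.

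**What to change.** 1. Reconcile Key study objectives, Outcomes and the data analysis plan so that all name a WAI-S time that is actually collected.
2. Summarise all T2 to T7 ratings by session and arm for every randomised participant with at least one session, and give the number contributing at each session.
3. Show T2 (post-session 1) by arm, split by whether the participant later completed treatment. This shows directly whether those who stopped began with lower alliance.
4. Use each participant's last completed rating as the overall summary and for interview selection. A descriptive mixed model with arm, session and their interaction is an alternative for the overall summary.

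The cost is analysis wording only. One small downside is that last ratings come from different session numbers; the by-session display makes this visible.
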